## Abstract

**Background:**

Currently recommended boosted protease-inhibitor (bPI) regimens may be associated with increased risk of cardiovascular or chronic kidney diseases; in addition, boosted regimens are particularly associated with drug-drug interactions. Since both cardiovascular and renal disease, and polypharmacy, are common in ageing people with HIV, there is a need for alternative efficacious regimens. bPI-based regimens are often the treatment of choice for individuals with pre-treatment or treatment-acquired resistance but it is plausible that carefully selected HIV-positive individuals with drug resistance, who are virologically suppressed on their current bPI regimen, could maintain virological efficacy when switched to bictegravir, emtricitabine and tenofovir alafenamide (B/F/TAF) fixed dose combination (FDC).

**Methods/design:**

A phase IV, investigator-initiated, multicentre, open label pilot, randomised two-arm study to assess the safety and efficacy of switching from bPI regimen to B/F/TAF single tablet regimen in integrase inhibitor-naïve, virologically suppressed adults with HIV-1 infection harbouring drug resistance mutations. Eligible individuals will either continue on their bPI regimen or switch to B/F/TAF FDC. After 24 weeks, all participants in the bPI arm will be switched to B/F/TAF and followed for a further 24 weeks and all participants will be followed for 48 weeks. The primary efficacy endpoint is the proportion of participants with HIV-1 RNA < 50 copies/mL at week 24 using pure virologic response whilst the secondary efficacy endpoint is the proportion of participants with HIV-1 RNA < 50 copies/mL at Week 48. Other secondary outcome measures include between arm comparisons of drug resistance at virological failure, safety and tolerability and patient-reported outcome measures.

**Discussion:**

We aim to provide preliminary evidence of the efficacy of switching to B/F/TAF in patients with virological suppression on a bPI-based regimen who harbour select drug resistance mutations.

**Trial registration:**

ISRCTN 44453201, registered 19 June 2019 and EudraCT 2018–004732-30.

## Background

Boosted darunavir and atazanavir are recommended as preferred boosted protease inhibitors (bPI) in the British HIV Association treatment guidelines. However, boosted darunavir was associated with increased cardiovascular risk in a large prospective observational study [1]. Although boosted atazanavir has not been associated with increased cardiovascular risk [2], cohort studies indicate an increased risk of chronic kidney disease [3]. In clinical trials, atazanavir recipients experienced higher discontinuation rates from adverse events than darunavir [2, 4] which were driven by hyperbilirubinaemia and renal events. Ageing of people living with HIV is resulting in increasing prevalence of cardiovascular and renal diseases; in addition, polypharmacy is common due to comorbidities, pointing to an additional limitation for bPI due to their particularly high potential for drug-drug interactions [5, 6].

There is evidence from clinical trials that switching from virologically suppressive bPI-based antiretroviral therapy (ART) to regimens based on the newer strand transfer integrase inhibitors, bictegravir [7] and dolutegravir [8] is safe and efficacious. These studies however excluded individuals known to harbour HIV-1 drug resistance. It is well established that HIV-positive individuals that have either pre-treatment drug resistance (PDR) or limited drug resistance following failure of first-line ART achieve virological suppression on regimens comprising a bPI plus two nucleos(t)ide reverse transcriptase inhibitor (NRTIs) [9, 10]. In contrast, in the SWITCHMRK study, switching virologically suppressed individuals from a bPI to the integrase inhibitor raltegravir resulted in an increased risk of virological failure relative to individuals maintained on the bPI. A post-hoc analysis suggested that this effect might be mediated by prior virological failure compromising the activity of the NRTI backbone [11].

However, evidence indicates that second-generation INSTIs, including bictegravir and dolutegravir, have an improved barrier to resistance relative to first-generation compounds and may overcome both PDR and limited treatment-associated drug resistance. In the DAWNING study, a second line switch to a regimen comprising the INSTI dolutegravir plus 2 NRTIs, where at least one NRTI was predicted to be fully active based on resistance analysis at the time screening, was superior to a bPI plus 2 NRTIs at 24 weeks in patients failing first line ART [12]. DAWNING study suggests second-generation INSTI like dolutegravir and by extension bictegravir are likely to be successful in switch strategies in the presence of either PDR or treatment-acquired drug resistance, including M184V/I or thymidine analogue mutations (TAMs). A small, open label, single arm study switched 37 patients (54% on a bPI-based regimen) harbouring the lamivudine (3TC) and emtricitabine (FTC) associated mutation M184V/I to the fixed dose combination (FDC) of elvitegravir/cobiscitat/emtricitabine/tenofovir alafenamide with no virological failures observed after 12 weeks of follow up [13]. Another study investigated whether efficacy was maintained following a switch to bictegravir/emtricitabine/tenofovir alafenamide FDC (B/F/TAF) in individuals suppressed on either a PI-based regimen or the FDC of dolutegravir/abacavir/lamivudine (DTG/ABC/3TC). Amongst the 572 participants on B/F/TAF, 532 (93%) achieved virologic suppression (VL < 50 copies/mL), with missing virologic data accounting for the majority of the remaining. Of the 572 participants, 405 (71%) had baseline resistance data available determined by both historical genotypes and baseline proviral DNA sequence; 52 (13%) of whom had NRTI associated resistance mutation present. 35/36 (97%) of those patients with archived F/TAF resistance mutations maintained HIV-1 RNA suppression through week 48 [14].

It should be noted that in virologically suppressed patients it is often possible to recover proviral sequences from cellular reservoirs in peripheral blood [14]. The presence of archived drug resistance mutations identified by sequencing proviral DNA is not necessarily reflective of the full range of resistant variants that may have emerged in an individual. Furthermore, it does not necessarily correlate with an increased risk of failure as integrated provirus is often defective [15] and reactivation of a particular virus is likely to be a stochastic event. In studies that examine drug activity in the presence of archived drug resistance, duration of follow up is crucial because the likelihood that a particular latent virus carrying a certain mutation would reactivate may increase with time, and the levels of adherence to ART over time play a key modulating role. In the single arm switch study referred to earlier, drug resistance sequencing based on proviral DNA missed half of M184V/I mutation present in historical genotype [13].

Taken together these studies suggest that B/F/TAF may be effective in maintaining virological suppression in patients with historical evidence of drug resistance mutations. In light of this, we hypothesize that switching HIV-positive patients who harbour selected drug resistance mutations and are virologically suppressed on bPI regimen to B/F/TAF will maintain virological efficacy over 24 weeks.

## Methods

### Trial design

The PIBIK trial is a phase IV, investigator-initiated, prospective, multicentre, open label pilot, randomised two arm study to assess the safety and efficacy of switching from a bPI-based regimen to B/F/TAF single tablet regimen in INSTI-naïve, virologically suppressed HIV-1 Infected adults harbouring drug resistance mutations. The allocation ratio is 1:1 (Fig. 1).

**Fig. 1 Fig1:**

Trial design

### Participants

Clinical staff in the HIV department will identify potential participants by any of the following methods: review of a clinic records/database, pre-identification of patients attending for routine care, review of notes during routine clinical follow up and posters/advertisements in the clinics to inform patients of the study.

Clinical staff identifying patients will be members of the direct care team or research nurses or doctors working within the same HIV multidisciplinary team. A medically qualified doctor on the study delegation log will confirm eligibility.

Anonymised information on participants who are not randomised / registered for CONSORT (16)reporting will include the reason, if they are not eligible for trial participation, or if they are eligible but declined.

Potentially eligible participants will be invited to attend for an appointment, having been provided with a participant information sheet (PIS). Adequate time will be allowed for questions and to consider the study before agreeing to participate. The investigator or designee will provide adequate explanation of the aims, methods, objectives and potential hazards of the study. It will also be explained to the individual that they are free to refuse or withdraw from the study for any reason without detriment to their future care or treatment. The investigator can decide to withdraw a subject from the study for urgent medical reasons or repeated non- compliance with the study protocol. Once randomised, withdrawn subjects may be replaced if considered necessary by the chief investigator.

#### Inclusion criteria

18 years and aboveOn a bPI-based ART regimen with documented HIV-1 RNA < 50 copies/mL for at least 6 months on current regimen and at screening (A switch from tenofovir disoproxil fumarate (TDF) to tenofovir alafenamide (TAF), lamivudine (3TC) to emtricitabine (FTC), or splitting co-formulated tablets to their individual component or vice versa will not be considered true regimen changes)Must have a historical genotypeEligible drug resistance mutations in historical genotype include at least one of the following:
o M184V/I with or without any NRTI-associated mutation (e.g. L74I/V, Y115F, K70E/G/Q/T/N/S)o M184V/I alone (maximum of 20 participants with isolated M184V/I mutation with or without NNRTI mutations)o Up to 2 TAMs (M41L, D67N, K70R, L210W, T215F/Y, or K219Q/E/N/R) with or without M184V/Io Any of the above with or without NNRTI mutationsNo previous use of any approved or experimental INSTINo known INSTI mutationsEstimated GFR ≥ 50 mL/min (Cockcroft-Gault formula)Have the following laboratory values at screening within 30 days prior to baseline:Alkaline phosphatase ≤3.0 x upper limit of normal (ULN)AST and ALT ≤5.0 x ULNHaemoglobin ≥9.0 g/dL (female) or ≥ 10.0 g/dL (male).

A single repeat of a laboratory screening test will be allowed for test results that are unexpected based on documented prior laboratory results.
Provides written, informed consent to participateIs willing to comply with the protocol requirementsIf a woman and of childbearing potential and are willing to continue practicing one of the following:
o Must be using effective birth control methods, that is has an expected failure rate of < 1% per year and willing to continue practicing these birth control measures during the trial and for at least 30 days after the end of the trial. Effective methods include IUD, combined pill, contraceptive injection, implant, IUS, contraceptive vaginal ring, contraceptive patches etc.o Must be truly abstinent from penile-vaginal intercourse from 2 weeks prior to administration of study drug, throughout the study, and for at least 30 days after the end of the trial (When this is in line with the preferred and usual lifestyle of the subject.) [Periodic abstinence (e.g., calendar, ovulation, symptothermal, post-ovulation methods), and withdrawal are not acceptable methods of contraception].Women who are postmenopausal for least 2 years, women with a total hysterectomy, and women who have a tubal ligation are considered of non-childbearing potential.If male, and sexually-active with female partners of child bearing potential, is using effective barrier contraception, and willing to continue using this during the trial and for at least 30 days after the end of the trial.

#### Exclusion criteria

Exclusion based on drug resistance mutations include
o Presence of any of the following mutations: K65R/N/Eo Presence of multidrug resistance mutations: T69ins, Q151M with or without A62V, V75I, F77L, F116Yo Three or more TAMs (M41L, D67N, K70R, L210W, T215F/Y, or K219Q/E/N/R)Individuals experiencing decompensated cirrhosis (e.g., ascites, encephalopathy, or variceal bleeding)An opportunistic illness within the 30 days prior to screeningActive tuberculosis infectionHave been treated with immunosuppressant therapies or chemotherapeutic agents within 3 months of study screening, or expected to receive these agents or systemic steroids during the study (e.g., corticosteroids, immunoglobulins, and other immune- or cytokine-based therapies)Current alcohol or substance use judged by the Investigator to potentially interfere with patients’ adherence to study procedure.A history of malignancy of less than 5 years or ongoing malignancy (including untreated carcinoma in-situ) other than cutaneous Kaposi’s sarcoma (KS), basal cell carcinoma, or resected, non-invasive cutaneous squamous carcinoma. Individuals with biopsy-confirmed cutaneous KS are eligible but must not have received any systemic therapy for KS within 30 days of Day 1 and are not anticipated to require systemic therapy during the study.Active, serious infections (other than HIV 1 infection) requiring parenteral antibiotic or antifungal therapy within 30 days prior to Day 1 (except if the parenteral therapy is for syphilis infection)Any other clinical condition or prior therapy that will, in the opinion of the investigator, make the patient ineligibleAny known allergies to the excipients of B/F/TAF FDCFemales who are pregnant (as confirmed by positive urine pregnancy test)Women who are breastfeedingWomen of childbearing age not using any reliable form of contraception (e.g. intrauterine device/intrauterine system, long-acting contraceptive injection)Acute hepatitis in the 30 days prior to study entry, anyone with hepatitis C (HCV) who is likely to need direct acting antivirals in studyAny concomitant medications that cannot be administered with TAF (i.e strong inducers of p-glycoprotein) or bictegravir (dofetilide, rifampins)

### Interventions

The investigational medicinal product in this trial is Biktarvy® comprising FDC of B/F/TAF. Each film-coated tablet contains bictegravir sodium equivalent to 50 mg of bictegravir, 200 mg of emtricitabine, and tenofovir alafenamide fumarate equivalent to 25 mg of tenofovir alafenamide.

Eligible individuals will either continue on their bPI regimen (arm 1) or switch to B/F/TAF FDC (arm 2). After 24 weeks, all participants in the bPI arm will be switched to B/F/TAF arm and will be followed up for a further 24 weeks whilst those immediately switched to B/F/TAF at baseline will be followed up for 48 weeks as illustrated in Fig. 1.

A participant is free to withdraw from the study at any time. In addition, the investigator may decide, for reasons of medical prudence, to withdraw a participant. If a participant discontinues study medication dosing, every attempt would be made to keep the participant in the study and continue to perform the required study-related procedures and follow-up procedures. If this is not possible or acceptable to the subject or investigator, the participant may be withdrawn from the study.

Study medication may also be discontinued in the following instances:
If the participant withdraws his/her consent.If the investigator considers in the interest of the subject (i.e. intercurrent illness, unacceptable toxicity) that it is best for them to withdraw their consent.The participant fails to comply with the protocol requirements or fails to cooperate with the investigator.Pregnancy during the course of the study.

The date and reasons for the withdrawal will be clearly stated on the participant’s eCRF and source document. Every attempt should be made to arrange follow up visits for participants who are withdrawn from the trial (including where individuals fall pregnant).

Participant adherence B/F/TAF and bPI will be assessed through:
Pill counting at each visit by a research team member and recording of the number of pills returnedSelf-report using a visual analogue scale (VAS)

Participants will bring in all pill bottles at each study visit. The total number of pills remaining at each visit will be counted and, then returned to the participant to take until the bottle is finished. The percentage of compliance for each participant will be calculated.

Participants will also be asked be asked to self-report their level of adherence at each visit using the VAS in which they would be asked to indicate their level of adherence in the previous 30 days on a scale ranging from 0 to 100% in which 0 represents no pill taken and 100 represents every single dose had been taken. Where adherence is < 80%, this will lead to likely withdrawal from the study although this will be at the discretion of the investigator.

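### Adherence below 80% is a likely reason to leave the study, so later rebound in low adherers who are still suppressed may go unseen and they count as responders

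*Protocol article*

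**What the plan says.** Three places in the protocol article bear on what happens to a participant who does not take the study drug as planned.

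- **Interventions, adherence paragraphs.** Adherence is measured by pill count and by a visual analogue scale at each visit. The consequence of a low value is: "Where adherence is < 80%, this will lead to likely withdrawal from the study although this will be at the discretion of the investigator". The text does not say which of the two measures triggers the rule.
- **Participants.** "The investigator can decide to withdraw a subject from the study for urgent medical reasons or repeated non- compliance with the study protocol". It adds: "Once randomised, withdrawn subjects may be replaced if considered necessary by the chief investigator".
- **Interventions, withdrawal paragraphs.** If dosing is discontinued, "every attempt would be made to keep the participant in the study and continue to perform the required study-related procedures and follow-up procedures". An exception follows: "If this is not possible or acceptable to the subject or investigator, the participant may be withdrawn from the study". The list of reasons for stopping study *medication* includes: "The participant fails to comply with the protocol requirements or fails to cooperate with the investigator". For those who do leave: "Every attempt should be made to arrange follow up visits for participants who are withdrawn from the trial".

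Outcome measures defines pure virologic response (PVR). Discontinuation for reasons other than rebound, with the last HIV RNA below 50 copies/mL and no data in the window, is a response. A value of 50 copies/mL or more followed by premature discontinuation is a rebound. The missing-data paragraph under Safety endpoints carries the last viral load forward to weeks 24 and 48. Allocation and blinding states that investigators and participants are not blinded.

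**The concern.** Adherence is observed after randomisation, and the protocol itself links it to the outcome. In studies of archived resistance, the Background says, "the levels of adherence to ART over time play a key modulating role", and it calls the duration of follow-up crucial. A rule that tends to end follow-up when adherence falls therefore selects on a variable tied to rebound, and people who know the allocation apply it.

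PVR keeps such a participant as a success if the last value was suppressed. Emergent resistance needs two consecutive values of 50 copies/mL or more, so it cannot be found in someone who is no longer sampled. At stake are the primary week-24 comparison, the rule that 45 of 50 on B/F/TAF must be suppressed for the study to continue, the week-48 response and the emergent-resistance outcome. In a non-inferiority trial, hidden failures in the switch arm push towards the conclusion the trial hopes to reach.

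**Working it through.** **1. The passages side by side**

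| Situation | Place | Consequence stated |
|---|---|---|
| Adherence below 80% | Interventions, adherence | Likely withdrawal from the study, at discretion |
| Repeated non-compliance | Participants | Investigator may withdraw from the study |
| Failure to comply | Interventions, list | Study medication may be discontinued |
| Dosing discontinued | Interventions | Keep in study if possible and acceptable |
| Already withdrawn | Interventions | Attempt follow-up visits |

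Read together, someone who stops every tablet is to be kept if possible, while someone just under 80% is likely to leave.

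**2. Who is affected**

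In Table 3, every visit with an adherence check also has an HIV-1 RNA (baseline, weeks 4, 12, 24, 28, 36, 48 and early termination).

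- Low adherence with RNA of 50 copies/mL or more, then withdrawal: PVR failure, so no bias.
- Low adherence at week 24: the endpoint sample is taken at that visit, so there is no bias in the primary endpoint.
- Low adherence at week 4 or 12 while suppressed, then withdrawal: scored as a response at week 24 unless a later sample is obtained.
- For week 48, the same applies at weeks 24, 28 and 36 as well.

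**3. The plan's own figure**

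For 90% in both arms, a margin of 13 points, 80% power and one-sided 10%:
n per arm = (1.2816 + 0.8416)² × 2 × 0.9 × 0.1 / 0.13² = 48.01, rounded up to 49, or 98 in total. This reproduces, and the point does not dispute it.

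**4. Overstatement in one arm**

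Assumptions, not in the protocol: k of 50 are withdrawn while suppressed because of low adherence, and each would have had chance f of rebound by week 24.

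Overstatement = k × f / 50
- k = 2, f = 0.2: 0.4/50 = 0.8 points
- k = 5, f = 0.6: 3/50 = 6.0 points

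**5. Effect on the 45/50 rule**

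P(X ≥ 45), X binomial with n = 50. If true B/F/TAF suppression is 85% (assumed):

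| Apparent rate | Overstatement | P(at least 45) |
|---|---|---|
| 85% | 0 | 21.9% |
| 86% | 1 point | 28.1% |
| 87% | 2 points | 35.4% |
| 89% | 4 points | 52.4% |

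This rule looks at one arm only, so nothing in the bPI arm offsets the effect.

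**6. Effect on the non-inferiority conclusion**

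Assumed truth at the margin: bPI 90%, B/F/TAF 77%, 50 per arm. The rule is a two-sided 90% Wald interval with lower bound above −13 points, enumerated exactly. Let w be the share of would-be failures withdrawn while suppressed and so scored as responders. The apparent rates are 1 − 0.10(1 − w) for bPI and 1 − 0.23(1 − w) for B/F/TAF.

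| w bPI | w B/F/TAF | Apparent rates | P(non-inferiority) |
|---|---|---|---|
| 0 | 0 | 90.0 / 77.0% | 5.5% |
| 10% | 10% | 91.0 / 79.3% | 8.0% |
| 25% | 25% | 92.5 / 82.75% | 14.5% |
| 0 | 25% | 90.0 / 82.75% | 22.4% |
| 25% | 0 | 92.5 / 77.0% | 2.7% |

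In the B/F/TAF arm, w = 25% hides 0.25 × 11.5 = 2.9 failures, close to the upper end of step 4 (5 × 0.6 = 3). The last row shows that the direction depends on which arm loses more failures. If both arms are raised by the same 6 points (96% and 83%), the difference stays at −13 points and the probability is 7.1%.

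**The case against.** The strongest case on the other side is that the protocol already limits the damage, and most of it stands.

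- A reader might infer that low adherers leave before they can fail. The documents do not support that. Withdrawal is likely, not automatic. Every adherence visit has a viral load, early termination carries its own HIV-1 RNA with resistance testing, and viraemic leavers are failures.
- A reader might infer a flat breach of the retention rule. The retention sentence covers people who discontinue dosing, it has an exception, and the Participants section separately permits withdrawal for repeated non-compliance. The conflict is one of purpose more than letter. But the exception is for cases where retention is not possible or acceptable, whereas the adherence rule makes leaving the likely outcome.
- A reader might infer that withdrawn participants drop out of the analysis or become wholly unobserved. Statistical analysis includes every randomised patient who took a dose, and follow-up visits are to be attempted after withdrawal. That attempt, however, is not a commitment to HIV-1 RNA at weeks 24 and 48.
- A reader might suppose that bPI pill counts are less exact, so that the trigger fires at different rates. Nothing in the text says so; both arms have the same pill count and scale.
- The harm to the primary endpoint works through the PVR and carry-forward rules. This is true, and those rules can be judged separately. What is distinct here is that the protocol itself can stop the sampling, and no later analysis can recover samples that were not taken.

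**Conclusion.** The point holds in a limited form and should be fixed. The sections give different answers on whether low adherence ends treatment, follow-up or both, and the decision lies with unblinded investigators. Following the adherence rule can hide later rebound and emergent resistance in participants who were suppressed when withdrawn, for the primary endpoint mainly at weeks 4 and 12.

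The size is unknown because the protocol gives neither the rate of adherence below 80% nor the rebound risk that follows. The range of 0.8 to 6 points for one arm rests wholly on the assumed 2 to 5 withdrawals and 20-60% risk. It should not be set directly against the 13-point margin, which concerns a difference between arms: withdrawals in both arms offset each other in part. The 45/50 rule has no such offset. The documents do not show that the trial's conclusion would be wrong, only that this rule can move it in the favourable direction.

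**What to change.** Reconcile the Participants section and the two parts of the Interventions section so that low adherence or non-compliance alone does not end follow-up. The wording should state that:

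- low adherence is recorded, with the measure that defines the 80% threshold named;
- any decision on study drug is separate from study participation and is not altered by this change;
- scheduled HIV-1 RNA, resistance and safety assessments continue to weeks 24 and 48 unless the participant withdraws consent or the investigator withdraws them for medical prudence, as Interventions already allows.

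The cost is protocol wording. A few poor adherers stay in visits that are already scheduled, and observed response may be slightly lower.
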